### Data Management and Monitoring

An independent data and safety monitoring board will be established to monitor the conduct and safety of the study. Two of our research team members will be responsible for updating our clinical trial–related information on the Chinese Clinical Trial Registry website and for making sure that no data are missed. However, if this becomes inevitable, we will use various processing methods to handle the issue. We will also perform a sensitivity analysis of the test results simultaneously.

### Adherence to Study Interventions

Throughout the study, patients will be given clear oral and written instructions to ensure proper adherence to the intervention. We will closely monitor their progress and provide personalized guidance when necessary. Any unused medication will be collected, documented, and returned as part of the study protocol.

### Data Analysis

Data analyses will be performed using SPSS 24.0 software. Continuous variables with a normal distribution will be analyzed using Student *t* test, while nonnormally distributed variables will be analyzed using the Wilcoxon rank sum test. Categorical variables will be analyzed using Pearson *χ*^2^ test. Continuous variables will be presented as mean (SD), while categorical variables will be presented as percentages. Values with *P* values ≤.05 will be considered statistically significant, and all tests will be 2-sided.

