### Randomization

Randomization will be conducted by an independent statistician using SPSS Statistics 26.0 (IBM Corp) software. A predetermined random number table will be generated, and 60 patients will be randomly assigned to either the intervention group or the standard-of-care group in a 1:1 ratio. To ensure accuracy and reliability, a random distribution table will be created in triplicate, with copies provided to the project leader, pharmacist, and statistician. The statistician, who remains blind to the trial and is not involved in patient recruitment, will generate the allocation sequence and securely store the master randomization list. Randomization will be implemented using a sealed envelope method to maintain allocation concealment. Each patient will receive a unique study identification number upon enrollment. The randomization table will be used to sequentially assign these numbers to either the intervention or control group. Each assignment will be enclosed in an opaque, sequentially numbered, and sealed envelope. After obtaining informed consent, the recruiter will open the envelope corresponding to the patient’s study ID and determine the group assignment.

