### Primary Outcomes

The primary outcome of this study is the incidence of SAP, which will be calculated using the following formula:

SAP incidence (%) = (number of SAP cases/total number of patients) × 100%

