### Secondary Outcomes

#### Modified Computed Tomography Severity Index

According to the analysis of the area under the curve, the modified computed tomography severity index demonstrates the highest accuracy in predicting SAP. It is a simpler and more accurate scoring tool, showing a stronger statistical correlation with factors such as length of hospital stay, development of infection, organ failure, and mortality [17,18]. It will be determined using the following formula:

Computed tomography severity index = (original score – current score)/original score × 100%

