#### APACHE II Score

The APACHE II (Acute Physiology and Chronic Health Evaluation II) scoring system has high sensitivity and exhibits a negative predictive value in predicting pancreatic necrosis and organ failure. This makes it an ideal prognostic tool for assessing the severity of AP and in guiding clinical decision-making, particularly in resource-limited countries [19]. It is determined using the following formula:

APACHE II = (original score – current score)/original score × 100%

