#### Modified Marshall Score

Organ failure plays a significant role in the severity of AP. The revised Atlanta classification recommends the use of the modified Marshall scoring system as the primary tool for assessing organ failure. The modified Marshall scoring system encompasses scoring systems for respiratory, cardiovascular, and renal systems to evaluate organ dysfunction in AP [6].

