### Sample Size

We will use preset sample sizes (*n*) determined using the following formula:

Where *μ*_1_ and *μ_2_* are the means of the intervention and placebo groups, respectively, and *σ* is the SD. The study aims to maintain the type I error probability (*α*) to <5% and the type II error probability (*β*) to <10%, with the *α* at .05 and the *β* at .1. To determine the sample size, we referred to literature reports in Chinese [24] on the use of DaXianXiong decoction for the treatment of AP. We used the time blood amylase took to return to normal levels to determine the clinical efficacy of the decoction. We fixed the total sample size for the study at 60. We allocated 30 patients to the intervention group and the remaining 30 to the placebo group.

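### The primary SAP comparison is an unadjusted chi-square test, although prognostic severity scores are scheduled at T0; adjusting for one of them would give a modest, nearly free gain in precision

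*Protocol article*

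**What the plan says.** The Primary Outcomes section states: "The primary outcome of this study is the incidence of SAP". (The Abstract lists more primary outcomes; I follow the Methods.) Each patient either has SAP or does not, so Data Analysis applies: "Categorical variables will be analyzed using Pearson" chi-square test, and "all tests will be 2-sided". The article names no covariate, regression model or stratified test.

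Table 2 schedules APACHE II, the modified CT severity index (CTSI) and the modified Marshall score at T0. The article describes them differently:

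- Modified CTSI: "the modified computed tomography severity index demonstrates the highest accuracy in predicting SAP".
- APACHE II: "This makes it an ideal prognostic tool for assessing the severity of AP", said of its ability to predict necrosis and organ failure.
- Modified Marshall: "Organ failure plays a significant role in the severity of AP". The section presents this score as the tool for assessing organ failure. It does not call it a predictor.

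Under Randomization: "A predetermined random number table will be generated, and 60 patients will be randomly assigned" in a 1:1 ratio. No severity stratum or minimisation is described. CTSI, APACHE II and the inflammation markers each have a percentage-change formula that uses the T0 value. The modified Marshall score has none.

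**The concern.** The trial plans to collect two scores that it regards as prognostic before treatment starts, and its primary test uses neither. Severity at entry probably matters here. The Introduction defines SAP by organ failure lasting at least 48 hours, recruitment is from an intensive care unit, and the eligibility criteria set no limit on the severity of the pancreatitis itself.

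With 30 patients per arm and no stratification, the arms can differ in entry severity by chance. An unadjusted comparison carries that difference into the estimated treatment effect. Adjusting for one baseline score removes part of this noise without further patients or procedures.

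The modified Marshall score has a related, lesser gap. With no change formula, the natural reading of Data Analysis is a comparison of post-treatment values that ignores the T0 value.

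**Working it through.** **Inputs from the protocol.** 30 per arm (Sample Size); "with the *α* at .05 and the *β* at .1" (Sample Size); two-sided tests (Data Analysis); about 20% of patients progress to SAP (Introduction); SAP roughly halved, reported for another drug class (Discussion).

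**Assumptions.** 20% v 10% combines the last two inputs. 40% v 20% is assumed for a sicker intensive-care population. The documents do not give the prognostic strength of the T0 score, so I take AUC 0.70 to 0.87.

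**The plan's own figure.** The sample of 60 cannot be reproduced, because the means and SD are not printed. At 30 per arm, two-sided 0.05 and 90% power, it corresponds to a standardised difference of (1.960 + 1.282) × √(2/30) = 0.837. That is for time to amylase normalisation, so the article states no power for SAP.

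**Power of the unadjusted test.** Power = Φ[(Δ − 1.96·SE₀)/SE₁], where SE₀ uses the pooled rate.
- 20% v 10%: SE₀ = √(2 × 0.15 × 0.85/30) = 0.0922; SE₁ = √((0.16 + 0.09)/30) = 0.0913. Power = Φ(−0.88) = 19%. Expected events: 30 × 0.20 + 30 × 0.10 = 9.
- 40% v 20%: SE₀ = √(2 × 0.3 × 0.7/30) = 0.1183; SE₁ = √((0.24 + 0.16)/30) = 0.1155. Power = Φ(−0.28) = 39%.

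**Chance imbalance.** The standardised difference in a baseline score has SD √(2/30) = 0.258.
- P(more than 0.25 SD) = 2[1 − Φ(0.968)] = 33%.
- P(more than 0.5 SD) = 2[1 − Φ(1.936)] = 5.3%.

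The resulting shift in the SAP difference is about ρ × √(0.15 × 0.85) × d, where ρ is the score–outcome correlation.
- At ρ = 0.3 (AUC about 0.73): 2.7 and 5.4 points for d = 0.25 and 0.5.
- At ρ = 0.5 (AUC about 0.87 to 0.89): 4.5 and 8.9 points.
- For a typical imbalance of 0.258 SD: 2.8 to 4.6 points, against a standard error of 9.1 points for the SAP difference.

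**Adjusting for one score, logistic model.** Simulation of 2,000 trials per setting, 30 per arm, one standard-normal composite score, likelihood-ratio test:

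| SAP rates | AUC | Chi-square power | Adjusted power | Variance cut |
|---|---|---|---|---|
| 20% v 10% | 0.71 | 19.0% | 21.7% | 4% |
| 20% v 10% | 0.79 | 20.7% | 25.5% | 19% |
| 20% v 10% | 0.87 | 20.3% | 29.0% | 29% |
| 40% v 20% | 0.70 | 38.4% | 44.6% | 9% |
| 40% v 20% | 0.79 | 36.9% | 47.3% | 18% |
| 40% v 20% | 0.86 | 40.4% | 57.5% | 37% |

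With no true effect, the likelihood-ratio test rejected in 5.1% to 6.7% of trials and the chi-square in 4.2% to 5.2%. The adjusted powers above are therefore somewhat flattered.

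**Adjusting for one score, linear model with robust standard error.**
- With the HC3 standard error, type I error was 4% to 5%. Variance fell by about 4% to 25% at SAP rates of 15% to 20%, and by 8% to 32% at 40%. Power at 20% v 10% went from about 19% to 18–21%.
- A second set of 20,000 trials per setting at ρ = 0.5 gave 19.1% to 22.5% at 20% v 10%, and 39.3% to 48.0% at 40% v 20%. Type I error was 4.7% to 5.3%.

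**Adjusting for all three scores separately (logistic).** Type I error rose to 6.0–8.5%, up to 9% of trials showed near-separation, and the variance cut was smaller than with one composite score in every setting.

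**The case against.** The strongest reply is that an unadjusted chi-square test is valid in a 1:1 randomised trial, and that chance imbalance is already part of its 5% error rate. This stands. A reader might infer that the planned test is biased or invalid, and the calculations do not support that. In the runs with no true effect, the chi-square rejected in about 9% to 26% of trials whose imbalance exceeded 0.5 SD. That figure is conditional on an event with 5% probability, rests on roughly 100 trials per setting (5% of 2,000), and averages out over all trials.

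Second, the size of the gain rests on a prognostic strength that no document gives. This also stands. A correlation of 0.5 is optimistic at these SAP rates, because it needs an AUC of about 0.87 or more. At the only rates drawn from the article, the gain may be nil.

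Third, an analysis plan that is not shown could add an adjusted analysis. It could, but the test that the article states is unadjusted, and that is what is assessed here.

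Fourth, a reader might infer that the protocol calls all three scores predictors, or that the 90% power applies to the modified Marshall score. Neither is supported: Marshall is described as a measure of organ failure, and the 90% belongs to amylase time. That raw Marshall values will be compared is also an inference from the missing formula.

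Finally, the Results section reports that data are collected and under analysis. Changing the primary test now could be a post hoc change. The fix has to allow for that.

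**Conclusion.** The point holds as a worthwhile improvement in efficiency. It is not an error that invalidates the trial. The stated primary test ignores a prognostic score already scheduled at T0, and nothing in the described randomisation balances severity.

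Adjusting for one score cuts variance by roughly 4% to 30% over the assumed AUC range; the most favourable logistic setting reached 37%. Power changes by about 0 to 10 points. I do not carry forward the 17-point rise in the last table row (57.5 − 40.4), because it needs the strongest score, the assumed 40% rate and the more liberal test.

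A reader might also infer that adjustment would rescue the primary comparison. It would not: at 20% v 10%, power stays near 20% to 30% with either analysis. The results assume a single, roughly normal score. The direction of the variance effect was the same in every one-score setting run; its size cannot be fixed from the documents.

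**What to change.** In Data Analysis, make the primary estimate an adjusted risk difference for SAP with a 95% CI and robust standard error. Take it from one named model containing treatment and a single T0 severity score. A linear probability model with the HC3 standard error held its type I error in the runs; a logistic model with standardisation is the alternative. Name only one of them.

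Name the score too: for example APACHE II, or modified CTSI, which the article itself credits with the highest accuracy. Do not enter all three, because only about 9 events are expected at 20% v 10%. Report the chi-square result alongside.

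Compare the modified Marshall score at each visit by ANCOVA with its T0 value as covariate. No power figure is claimed for this.

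Fix the wording before unblinding and record the date. If the data have already been unblinded, keep the chi-square as primary and label the adjusted analysis supportive and post hoc.

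The cost is a few lines of text, one degree of freedom and a less familiar primary test. With the HC3 standard error there may be no gain in power at low SAP rates. No new data, visits or patients are needed.

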### Frequency and Plans for Auditing Trial Conduct

The trial conduct will be audited at specified frequencies by an independent team that does not include the investigators and sponsor. The details of the auditing frequency and plans are provided in Table 2.

### Ethical Considerations

This study protocol involving human patients was reviewed and approved by the Chongqing Traditional Chinese Medicine Hospital on September 6, 2022 (2023-KY-52).

Patients will be provided with a consent form with a clear outline of the use of their data, allowing them to choose whether to continue participating or withdraw from the trial. Biological specimens collected for storage will be handled according to ethical guidelines, and they will be destroyed after their intended use. Patient privacy will be strictly maintained. Physical documents related to the study will be secured in a locked office.

### Modification of the Protocol

Any modifications to the program will require the consent of both the project leader and the supervisor. After obtaining approval from the ethics committee, the sponsor and all members of the research team will be notified of the changes.

## Results

This study has been funded by the Performance Incentive Project of Scientific Research Institutions in Chongqing. The trial was registered in April 2024, and data analysis is expected to be completed by April 2025. The recruitment for the trial commenced in December 2023. The data has been collected and is being analyzed. The study results will be presented at both national and international conferences and published in peer-reviewed journals.

## Discussion

### Expected Findings

This study aims to evaluate the efficacy and safety of DaXianXiong decoction in preventing the progression of AP to SAP by conducting a randomized, double-blind, placebo-controlled, single-center trial. The treatment of SAP continues to be a challenge, and preventing the progression of AP to SAP has been a hot spot of research in critical care medicine and gastrointestinal diseases. Inflammatory cascade-driven response is considered to be an important cause of progression to SAP in patients with AP combined with organ failure [25]. Inflammatory response to AP triggers visceral edema and gastrointestinal dysfunction, leading to increased abdominal pressure and possible abdominal septal compartment syndrome and organ failure [26]. Among the studies on blocking the progression of AP to SAP, Huang et al [27] observed that cyclooxygenase 2 (COX-2) inhibitors (parecoxib and celecoxib) reduced serum tumor necrosis factor–α and IL-6 levels in patients with AP, reducing the incidence of SAP by approximately half. He et al [28] observed that neostigmine reduced AP and abdominal pressures and facilitated defecation, thereby reducing the incidence of organ dysfunction in patients with AP. However, these drugs have a single therapeutic target and have potential risks, such as COX-2 inhibitors that may lead to gastrointestinal mucosal damage or even gastrointestinal bleeding, and neostigmine that may cause bradycardia and increase airway resistance.

DaXianXiong decoction has been commonly used in Asia for the treatment of AP for more than 30 years [29,30]. In our study, we used DaXianXiong decoction in addition to conventional treatment to observe its efficacy in preventing the progression of AP to SAP. The key advantage of this study compared with previous studies is that DaXianXiong decoction has the advantage of being multi-targeted to simultaneously act to improve gastrointestinal function and reduce the inflammatory response, which has the potential to block the progression of AP. In addition, this study may pave the way for larger multicenter trials to further investigate the potency and cost-effectiveness of complementary treatment strategies in larger populations.

### Limitations

The study has limitations because of the small sample size. Additionally, the mechanism path of DaXianXiong decoction remains unclear and requires further investigation. However, these limitations provide further opportunities for expanding the findings and gaining a deeper understanding of the treatment.

## Appendix

Multimedia Appendix 1 SPIRIT checklist.

Multimedia Appendix 2 Informed consent.

## Abbreviations

AE: adverse event
AP: acute pancreatitis
APACHE II: Acute Physiology and Chronic Health Evaluation II
COX-2: cyclooxygenase 2
IL: interleukin
SAP: severe acute pancreatitis
SPIRIT: Standard Protocol Items: Recommendations for Interventional Trials
